#### Correlates of Energy Misestimation

Psychosocial, demographic, and cognitive factors associated with omission and intrusion rates and with energy misestimation on each 24HR method will be evaluated using chi-square tests and multivariate logistic regression. The effects of factors will be reported as odds ratios and associated 95% CIs. Some dietary factors in the Accuracy and Cost-effectiveness of Technology-Assisted Dietary Assessment study are standardized because of the controlled feeding methodology (meal frequency and eating location), but it is hypothesized that food and meal complexity and physical form will affect reporting accuracy via an interaction with cognitive factors. P<.05 will be considered statistically significant in all analyses.

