### Objectives

This research protocol will compare 3 leading technology-assisted dietary assessment methods. Using a controlled feeding study design with healthy adults aged 18 to 70 years, this study will (1) compare the accuracy, acceptability, and cost-effectiveness of 3 technology-assisted 24HR methods (ASA24, Intake24, and mFR24) relative to observed intake for 3 meals on 1 day; (2) test the accuracy of automated methods for determining food and beverage intake using food images and image analysis, computer vision, and machine learning techniques; and (3) assess associations between reporting errors and demographic, psychosocial, and cognitive factors.

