**Figure 2 figure2:**
[figure not shown]
Conceptual framework for assessment of factors that may be associated with 24-hour dietary recall reporting accuracy. 24HR: 24-hour dietary recall.

**Table 1 table1:** Baseline study questionnaire and test descriptions in Accuracy and Cost-effectiveness in Technology-Assisted Dietary Assessment.

Questionnaires and tests			Description of content		Study
Demographic and personal characteristics			11 items: gender, age, educational level, employment, country of birth, ethnicity, smoking, alcohol use, and socioeconomic and financial status		—^a^
Physical activity			8 items: International Physical Activity Questionnaire (short form)		[49]

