Matches between reported and observed intake will be identified by comparing the assigned food codes. Food codes correspond to a food grouping hierarchy in which the first 2 digits indicate the major food groups (eg, dairy, meat, and vegetables), the first 3 digits indicate the submajor food groups (eg, milk products and dishes), and the first 5 digits indicate the minor food groups (eg, dairy milk, yogurt, and cheese) [77]. Food codes of reported and observed intake data will be considered an exact match if they belong to the same minor food group. Foods codes from the same submajor food group will be considered a close match, whereas foods from the same major food group will be considered a far match.Omissions, which are items that were consumed but are not reported, will be identified, and omission rates at each food group level will be calculated using the formula:sum of omissions / (sum of omissions + sum of all matches) × 100%.Omission rates of mixed meals, single items, and condiments will be calculated. Differences in omission rates by 24HR method will be assessed using chi-square tests.The proportion of misclassifications, which are incorrect descriptions of consumed items, will be defined as close or far matches. Differences in the proportion of misclassifications within food groups by the 24HR method will be assessed using chi-square tests.Intrusions, which are items that are reported but were not consumed, will be identified, counted by food group, and expressed in kilojoules.Misestimation of portion size will be assessed by comparing the intake of food item matches in grams for each 24HR method with observed intake using a paired samples statistical test.

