## Discussion

### Overview

This study will provide outcome results in 3 main areas. It will evaluate (1) the accuracy, user acceptability, and administration cost of 3 technology-assisted dietary assessment tools, which have never been compared in a single study; (2) the accuracy of novel automated image analysis technology; and (3) the association of reporting accuracy of participants with a range of cognitive and psychosocial factors.

The results of this research will provide additional information on the feasibility, accuracy, and cost to aid the selection and further development of 3 technology-assisted 24-hour recall methods for application in large-scale dietary assessment. The use of a controlled feeding study design for comparing multiple technology-based dietary assessment methods is novel and will allow comparison among methods relative to observed intake. The results will also elucidate the correlates of dietary intake misreporting, which will be useful in developing error mitigation strategies.

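### The search for correlates of misreporting applies P<.05 to roughly 180 to 252 tests without false-positive control or an exploratory label, so about 9 to 13 false-positive tests are expected if no factor is related to misreporting.

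*Protocol article*

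**What the plan says.** The rule stands at the end of Data Analyses, Correlates of Energy Misestimation: "P<.05 will be considered statistically significant in all analyses". The same section defines the search: "Psychosocial, demographic, and cognitive factors associated with omission and intrusion rates and with energy misestimation on each 24HR method will be evaluated". The tools are chi-square tests and logistic regression, with odds ratios and 95% CIs to be reported.

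Under Food Groups and Misreporting, omission rates are calculated at the food-group levels and compared by method. In addition, "Differences in the proportion of misclassifications within food groups by the 24HR method will be assessed using chi-square tests". Portion sizes of matched items are tested against observed intake for each method.

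Associations with reporting error are the third aim under Objectives, and the Discussion's Overview lists them among the study's three main result areas. It adds: "The results will also elucidate the correlates of dietary intake misreporting, which will be useful in developing error mitigation strategies".

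The article names no multiplicity adjustment or false discovery control, and no order of priority among factors or outcomes. Within Data Analyses, the only exploratory wording is under Acceptability, and it concerns preference for a method.

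**The concern.** The article goes further than leaving multiplicity unmentioned. It gives a decision rule and extends it to every analysis. Followed as written, the rule yields a list of significant factors even if nothing measured is related to misreporting. A reader could not tell which entries are chance.

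This matters because the correlates are presented as a main result and are meant to guide ways of reducing reporting error. A mitigation strategy built on a chance finding would be wasted effort.

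**Working it through.** The article gives no test count or error rate to reproduce, so the count has to be built from its text.

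**Inputs**

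- Level per test: 0.05 (Correlates of Energy Misestimation).
- Outcomes: 3, namely omission rate, intrusion rate and energy misestimation (same section).
- Methods: 3 (Objectives).
- Cells (outcome by method): 3 x 3 = 9. If the reference to each method attaches only to energy misestimation, 1 + 1 + 3 = 5.
- Factors (Table 1): 11 demographic items, of which 10 are named; 1 physical activity instrument; 6 psychosocial instruments, or 8 scores if the eating questionnaire counts as three subscales, or 9 if the two weight-loss items are also split; 4 cognitive tests, or 5 with digit span forward and backward apart, or an assumed 7 with further sub-scores.

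**Expected false positives if no factor is related** = factors x cells x 0.05, counting one test per factor per cell.

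| Factors (demographic + activity + psychosocial + cognitive) | 9 cells: tests | Expected | 5 cells: tests | Expected |
|---|---|---|---|---|
| 10 + 0 + 6 + 4 = 20 | 180 | 9.0 | 100 | 5.0 |
| 11 + 1 + 6 + 4 = 22 | 198 | 9.9 | 110 | 5.5 |
| 11 + 1 + 8 + 4 = 24 | 216 | 10.8 | 120 | 6.0 |
| 11 + 1 + 8 + 5 = 25 | 225 | 11.25 | 125 | 6.25 |
| 11 + 1 + 9 + 7 = 28 | 252 | 12.6 | 140 | 7.0 |

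Correlation between tests does not change these expectations. It does change their spread: for 225 tests, the chance of at least one false positive is about 1.00, 0.92 and 0.43 at assumed common correlations of 0, 0.5 and 0.8.

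**Tests versus distinct factors.** With 25 factors and nine independent tests each, the expected number of factors with at least one false positive is 25 x (1 - 0.95^9) = 25 x 0.370 = 9.2. As the nine tests on a factor become more positively correlated, this falls towards 25 x 0.05 = 1.25.

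**Food groups.** The number of groups is not given. Assuming 5 to 24 groups, one omission and one misclassification test per group give 10 to 48 tests, or 0.5 to 2.4 expected false positives at a true 5% level. Adding a portion-size test per group and method gives 25 to 120 tests and 1.25 to 6.0. This is only an illustration. The chi-square tests compare items reported by the same participants under three methods, so their nominal level may not be 5%.

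**The case against.** **The sentence does not say the P values are unadjusted.** A P<.05 threshold is literally compatible with adjusted P values, and an article may leave adjustment to an unseen analysis plan. That is true of the wording. But the article mentions no adjusted P value, and the sentence closes the section that defines the search and covers all analyses. The natural reading is the nominal level.

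**The counts are assumed.** This stands. Items may be dropped or combined, physical activity may not count as a factor, and the narrower reading gives five cells. Each figure is therefore a range. On none of these readings is the expected number below 5.

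**A reader might infer that about 11 spurious correlates will be named.** The documents do not support that. The 10.8 to 11.25 obtained with 24 or 25 factors counts tests. Omissions and intrusions feed into energy misestimation, so one factor can be flagged in several cells. A reader might also infer that the food-group tests run to hundreds. The article gives no number of groups, and the size of the problem rests on the correlates alone.

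**The case of no association is the worst case.** The Introduction cites a study in which psychosocial and demographic factors accounted for 20% of the variability in misreporting. This is fair: the expected count is 0.05 times the number of true nulls, so if half of 216 tests were null it would be 108 x 0.05 = 5.4. The difficulty of telling real findings from chance would remain.

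**Leaving a search for correlates unadjusted is a matter of judgment.** It is defensible when the search is labelled exploratory, which this one is not. The promised odds ratios with 95% CIs help on magnitude but do not change the significance rule.

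**Conclusion.** The point holds in a limited form. The article fixes P<.05 for the correlate analyses, presents them as a main result, and neither controls false positives nor calls the analyses exploratory. About 9 to 13 false-positive factor-by-outcome-by-method tests are expected, or 5 to 7 on the narrower reading. This assumes 20 to 28 factors, one test per factor per cell, tests that keep their 5% level, and no true association. The number of distinct factors wrongly flagged would generally be smaller. Food-group tests add a number that the article does not allow anyone to fix.

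The main comparison of energy accuracy between methods is not affected. What is at stake is the credibility of the third objective and of the food-group findings, which justifies a change of wording before analysis.

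**What to change.** Keep the existing P<.05 sentence. Deleting it would leave the energy-accuracy and acceptability analyses without a stated level, since only Cost-effectiveness repeats one. Add an exception directly after it, to this effect:

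> The correlate analyses and the food-group tests (omission, misclassification and, if done by food group, portion size) are exploratory. Benjamini-Hochberg false discovery rate control at 5% will be applied within each family: factors within each outcome over the three methods, and food-group tests within each error type. It will use P values from methods valid for repeated measures on the same participants. Odds ratios or differences will be reported with 95% CIs and adjusted P values. Associations that do not survive adjustment will be described as hypothesis-generating.

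Qualify the claim about correlates in the Discussion's Overview in the same way. The validity condition matters because false discovery control applied to P values that ignore the repeated measures would not deliver the stated rate.

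The cost is a short paragraph and a little code. Analysis was planned to begin in 2022, after publication of the article, so the change could precede it. The downside is some loss of power for weak true correlates. It is milder than Bonferroni, which over 216 tests would require 0.05/216 = 0.00023 per test.

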#### Acceptability

Differences in acceptability among methods indicated by the rating and proportions of participants agreeing with each of the ease-of-use statements will be assessed using chi-square tests. Demographic correlates of a preference for a particular method will be explored using multivariable logistic regression, adjusting for method order.

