## Methods

### Sample and Recruitment

The sample will be selected from adults aged 18-70 years residing in Perth, the capital city of Western Australia, Australia, and recruited via the electoral roll by selecting postcodes that provide representation across socioeconomic status. Other recruitment methods will include advertising on the Curtin University website and a snowball methodology (eg, email newsletter and referrals from friends or colleagues). A final sample of 150 randomized participants (allowing for a 20% dropout) will allow for 90% power at a 5% significance level when the true difference between any 2 mean differences between estimated and observed dietary energy intake is 0. Quota sampling will be used to ensure that equal numbers of men and women are recruited. To be included in the study, participants must be able to attend in-person feeding sessions on 3 separate days and have access to a computer and a smartphone (running iPhone operating system or Android operating system) with a data plan. Exclusion criteria include serious illnesses or medical conditions, pregnancy, special dietary requirements, or dietary restrictions because of food allergies or intolerances or dieting to lose weight.

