### Study Design

A controlled feeding study with a crossover design will compare the accuracy of 3 technology-assisted methods of assessing 1 day of dietary intake: ASA24, Intake24, and mFR24. The sequence of the 3 dietary assessment periods will be randomized for each participant, with a 1-week washout period between each feeding session (Figure 1). Therefore, each participant will be exposed to each of the 3 methods at different periods. The crossover design, a repeated measurement design, will allow both between-group and within-group method comparisons. This design yields a more efficient comparison of treatments than a parallel design because fewer participants are required in the crossover design to attain the same level of statistical power or precision as a parallel design.

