### Poststudy Acceptability Questionnaire

The participant’s perceptions of the acceptability of the 24HR method will be asked at the end of the study via a web-based survey using both open and closed questions. Their perceptions of each method will be asked about one at a time in a randomized order. Participants will be asked what device they used to complete each method and then be asked questions using a 5-point Likert scale to rate their agreement with statements including how easy it was to find and remember foods and remember amounts and whether they would be willing to use the method again. Open-ended questions will explore the participant’s likes and dislikes about each method. Finally, participants will be asked which of the methods, if any, they preferred and why.

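### The 5-point acceptability ratings are to be compared by chi-square tests, which use neither the order of the scale nor the fact that each participant rates all three methods

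*Protocol article*

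**What the plan says.** Under Poststudy Acceptability Questionnaire, participants are asked about each 24-hour recall method in turn and will "be asked questions using a 5-point Likert scale to rate their agreement with statements" on matters such as ease of finding foods and willingness to use the method again. Under Data Analyses, Acceptability, the plan reads: "Differences in acceptability among methods indicated by the rating and proportions of participants agreeing with each of the ease-of-use statements will be assessed using chi-square". The rating is named separately from the proportions, so two comparisons are planned for each statement: one on the full 5-level scale and one on agreement. Study Design confirms that "each participant will be exposed to each of the 3 methods at different periods". The significance level is fixed under Correlates of Energy Misestimation: "P<.05 will be considered statistically significant in all analyses". The Acceptability section names no ordinal, rank-based or paired method for the ratings. Its only regression concerns which method is preferred.

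**The concern.** Comparing acceptability is part of objective 1, and it is an ordered question: which method is rated higher, and by how much. A chi-square test on a table of 3 methods by 5 answers gives the same result however the five columns are rearranged. It spreads its sensitivity over 8 degrees of freedom, although a shift between three methods needs only 2.

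It also assumes that the three rows come from different people. Here the same people fill all three rows. If someone who rates one method highly tends to rate the others highly, differences between methods vary less than the test assumes. The test then becomes conservative and gives up the within-person precision that Strengths and Limitations presents as an advantage of the crossover.

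At stake is a missed difference in acceptability that the data could have shown, or a significant result that does not say which method people find more acceptable.

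**Working it through.** **The plan's own figure.** Sample and Recruitment says: "A final sample of 150 randomized participants (allowing for a 20% dropout) will allow for 90% power at a 5% significance level". The dropout step is consistent: 150 × (1 − 0.20) = 120. The 90% power refers to energy intake. It cannot be reproduced, because the true difference is given as 0 with no standard deviation or margin. No power is stated for acceptability, so there is no figure for the ratings to reproduce.

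**Inputs.** From the article: 3 methods, 5 ordered categories, 120 completers, 5% level, all methods rated by each participant. Assumed, because the article does not give them: base ratings of 8/15/20/35/22%; a proportional-odds shift δ with the methods at 0, δ/2 and δ; within-person correlation ρ of 0, 0.3 or 0.5 on a latent normal scale.

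**Formulas.**
- Shift: logit P(Y ≤ k) = base logit − (0, δ/2 or δ).
- Pearson: X² = Σ(O − E)²/E. Degrees of freedom are (3 − 1)(5 − 1) = 8 for the rating and (3 − 1)(2 − 1) = 2 for agree or not.
- Comparators: Kruskal-Wallis (ordered, unpaired, 2 df) and Friedman with mid-ranks within participant (ordered and paired, 2 df).

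**Ceiling for the degrees of freedom alone.** For equal noncentrality, the gap between 2 and 8 df is largest at a noncentrality of 7.9: 71.2% against 47.1%, or 24.1 points.

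**Simulated power (%), 3,000 trials per row.**

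| ρ | δ | Chi-square 3×5 | Agree 3×2 | Kruskal-Wallis | Friedman |
|---|---|---|---|---|---|
| 0 | 0.2 | 7.4 | 9.6 | 10.7 | 9.5 |
| 0 | 0.5 | 26.9 | 37.1 | 47.6 | 42.2 |
| 0 | 0.6 | 39.3 | 49.7 | 62.0 | 55.8 |
| 0 | 0.7 | 52.9 | 63.4 | 76.9 | 70.8 |
| 0 | 1.0 | 87.1 | 90.3 | 97.3 | 95.5 |
| 0.3 | 0.5 | 21.2 | 32.3 | 42.8 | 53.4 |
| 0.3 | 0.6 | 35.2 | 48.6 | 62.9 | 72.2 |
| 0.3 | 0.7 | 49.3 | 63.2 | 79.4 | 84.3 |
| 0.5 | 0.5 | 17.5 | 29.4 | 40.5 | 67.9 |
| 0.5 | 0.6 | 30.6 | 47.3 | 61.9 | 83.9 |
| 0.5 | 0.7 | 47.0 | 61.2 | 80.0 | 93.8 |

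**Losses.**
- Order alone (ρ = 0, 3×5 against Kruskal-Wallis): 10.7 − 7.4 = 3.3 points at δ = 0.2; 20.7, 22.7 and 24.0 at 0.5, 0.6 and 0.7; 97.3 − 87.1 = 10.2 at 1.0.
- Agree 3×2 against Kruskal-Wallis (ρ = 0): 10.5, 12.3 and 13.5 points at 0.5, 0.6 and 0.7.
- Order and pairing (3×5 against Friedman): 32.2, 37.0 and 35.0 points at ρ = 0.3; 50.4, 53.3 and 46.8 at ρ = 0.5.

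**Type I error (δ = 0).** The 3×5 test rejects in 5.2%, 3.3% and 2.0% of trials at ρ = 0, 0.3 and 0.5. Friedman rejects in 5.3 to 5.9%.

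**Spread only.** Two methods keep the base ratings and the third has 16/13/9/30/32%.
- Means: 0.08 + 0.30 + 0.60 + 1.40 + 1.10 = 3.48, against 0.16 + 0.26 + 0.27 + 1.20 + 1.60 = 3.49.
- Agreeing: 35 + 22 = 57%, against 30 + 32 = 62%.
- With independent ratings, the 3×5 test rejects in 79% of trials, Kruskal-Wallis in 9% and the agree test in 11%.

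**The case against.** The strongest reply is that the rating test is only half of what is planned. The comparison of proportions agreeing has direction, needs only 2 degrees of freedom, and in the spread-only example behaves much like the rank test. This stands, and it softens the consequence: a reader might infer that the plan has no directional test of acceptability, which the text does not support. It does not remove the point. The agree test discards strength of agreement, has less power than a rank test at moderate shifts, and is also unpaired as written.

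Second, a reader might take a loss of about 25 points as a property of this trial. The article gives no rating distribution or shift of interest, and 25 is close to the maximum for independent ratings. The loss is small for small and very large shifts.

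Third, a reader might call rejection for a polarising method a false positive. It is not. The distributions differ, the test detects that correctly, and a wider spread could matter in practice. A proportional-odds model would be poorly suited to finding it. What remains is that such a result does not rank the methods.

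Finally, the sample size does not rest on acceptability, which is also covered by stated preference, open questions and exit interviews. That limits the weight of the point but does not make the test suitable.

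**Conclusion.** The point holds in a limited form. The article assigns chi-square tests to an ordered, within-person rating. On the full scale, that choice uses neither the order nor the pairing.

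The size is illustrative and rests on the assumed base ratings, 120 completers and proportional-odds shifts. With independent ratings the loss is about 3 points at a log odds ratio of 0.2, up to about 25 at 0.5 to 0.7 and about 10 at 1.0. For the agreement test it is about 11 to 14 points at 0.5 to 0.7. With within-person correlation of 0.3 to 0.5, which the article neither states nor rules out, the full-scale test loses about 32 to 53 points against a paired rank test, and its type I error falls to about 2 to 3%. The error is therefore towards missing differences, not towards false claims.

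This is a worthwhile correction to one component of objective 1. It does not affect the accuracy comparison.

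**What to change.** In Data Analyses, Acceptability, replace the chi-square test on the ratings with a cumulative-logit mixed model for each statement: method and method order as fixed effects, participant as random effect, and pairwise odds ratios with 95% confidence intervals. A Friedman test is a simple alternative if a model is not wanted. Keep the comparison of proportions agreeing, which is easy to interpret, but analyse it as paired, by Cochran's Q or by a mixed or GEE logistic regression. Showing the full distribution of ratings by method would keep any difference in spread visible.

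The cost is a few sentences of analysis wording, slightly more analysis work and a proportional-odds assumption to check. No new data are needed.
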